**6. SPECIFIC AIMS**

**Primary Aim 1:** Evaluate the feasibility and acceptability of ROC and CBT.

**Primary Aim 2:** Compare the efficacy of ROC and CBT on binge eating over the duration of the study.

**Primary Aim 3:** Compare the efficacy of ROC and CBT on weight loss (BMI) and energy intake (as measured by 24-hour dietary recalls) over the duration of the study.

**Secondary Aim 1:** Determine the extent to which ROC and CBT influence underlying mechanisms of action, including responsivity to food cues, satiety responsiveness, and reward-based eating.

**Exploratory Aim 1:** To evaluate moderators of treatment (age, gender, binge eating status, satiety responsiveness, responsivity to food cues, reward-based eating) and mediators of treatment outcomes (responsivity to food cues, satiety responsiveness, reward-based eating, physical activity).

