## **Research Design and Methods**

**Study Overview.** This proposal is a randomized controlled study with two arms: ROC and CBT. The ROC program targets improved satiety responsiveness and decreased food responsiveness and provides psychoeducation (ways the environment “tricks” the body into overeating past nutritional needs, coping skills designed to assist in mastery and toleration of food cue sensitivity, daily self-monitoring (hunger, satiety, and cravings)) and experiential learning (exposure sessions while self-monitoring hunger, satiety, and cravings). Additionally, the ROC participants will be taught to decrease caloric intake and increase physical activity, to assist with satiety responsiveness and to decrease food cue responsiveness. The CBT treatment program focuses on disrupting the restraint/binge cycle by improving maladaptive thoughts surrounding eating, shape, and weight. As part of CBT, participants self-monitor food intake, to understand the thoughts that trigger binge eating and as a way to identify times of restriction that can trigger binge eating. CBT targets explicit urges to binge eat but does not include experiential exercises. (See Table 1)

We will recruit 300 overweight and obese male and female Veterans with BED or subclinical BED to randomize at least 120 meeting all inclusion criteria, will provide 5 months of treatment and will follow participants for 6 -months post-treatment. Total length of participation will be approximately 11 months. Participants will complete assessments at baseline, mid-treatment (~week 10), post-treatment (week 20), and 6-month follow-up (week 44). Participants will complete brief survey assessments monthly during treatment to assess mediators. We will also collect data on feasibility and acceptability of the two treatments. In person assessments will take 3-4 hours except for the mid treatment which will be about 1 hour. This study is being conducted in collaboration with investigators from the VA San Diego Healthcare System (VASDHS). The collaborators will file a separate IRB proposal through the VA to cover their research activities which will include directly recruiting Veterans from health clinics at the VA and conducting the initial screen. Information collected in their screen will securely be shared with our research team. UCSD team will complete the remainder of screening, assessments and treatment of the participants.

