### **Measures**

***A complete summary of the list of assessment measures and time points administered are provided in Table 2. The primary outcome measures are provided in more detailed below.***

***Psychiatric symptoms (baseline only).*** Participants will complete the Mini-International Neuropsychiatric Interview (MINI) to confirm eligibility at baseline (i.e., absence of exclusionary psychiatric condition). The MINI 7.0 is a short, structured diagnostic interview developed to assess psychiatric disorders according to DSM-5 criteria, focusing on current symptomatology.

***Medical diagnoses and medications.*** Participants will report any known medical diagnoses and current and past medications to confirm eligibility at baseline. We will follow-up monthly during treatment to see if any changes have occurred and again at follow-up.

***Demographics and military characteristics (baseline only).*** Participants will complete a demographic questionnaire to record their age, gender, years of education, socioeconomic status, branch of service, years and position in military, highest rank at discharge, and years since actively serving in the military.

***The Eating Disorder Examination (EDE) interview*** (baseline, mid-treatment, post-treatment, 6-month follow-up) is considered the gold-standard assessment for BED and has strong psychometric properties. The EDE interview uses diagnostic algorithms to diagnose BED, as well as subclinical BED, frequency of binge eating, compensatory behaviors (purging for exclusion), as well as restraint and shape and weight concerns.

***The Binge Eating Scale*** (BES) (baseline, mid-treatment, post-treatment, 6-month follow-up) provides a dimensional score of binge eating. The BES consists of 16 items; 8 items describe binge eating behaviors and 8

describe feelings and cognitions associated with binge eating. The BES yields a continuous measure of binge eating pathology (range=0–46).

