**Primary Aim 2:** Efficacy of ROC and CBT on changes in binge eating (*as measured by the EDE; EDE-Q and BES*), at mid-treatment, post-treatment and 6-months post-treatment timepoints. LME models with dummy-coded indicators for planned treatment comparisons between ROC and CBT, and a continuous term for time selected after evaluating non-linearity. Between-group (ROC vs. CBT) differences in change in binge eating (Primary Aim 2) will be estimated in models with planned covariates (age, gender), baseline BMI, and corresponding baseline values for each outcome. The GLME for counts of binge episodes and LME model for continuous symptom inventories provide maximum likelihood parameter estimates based on all of the available data, allowing for the inclusion of cases with missing data and the modeling of the covariance error structure of the data across the assessment points. Interactions of between-group indicator and time will assess whether differences in binge eating dissipate from active treatment compared to the 6-month follow-up timepoint.

**Primary Aim 3:** Efficacy of ROC and CBT on changes in weight loss (BMI) and energy intake (kcal/day), at mid-treatment, post-treatment and 6-months post-treatment time points will be evaluated with (G)LME models. Between-group (ROC vs. CBT) differences in change in BMI and energy intake will be estimated in models with planned covariates (age, gender), and corresponding baseline values for each outcome.

**Secondary Aim 1:** Efficacy of ROC and CBT on changes in food responsivity (FR scale; psychophysiological responding to food, reward-based eating) and satiety responsiveness (SR scale, WLT), using GLME adjusted for corresponding baseline values and planned covariates mirroring primary analyses. We also will use (G)LME to assess between-group differences in measures of reactivity to food cues using psychophysiological measures of EMG (salivation), heart rate and HRV at each follow-up.

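### Primary Aim 2 rests on three unranked binge-eating instruments with no lead outcome or deciding contrast, and the Measures section attaches the primary label to measures that serve other aims

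*Protocol*

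**What the plan says.** Section 6 states the aim without an instrument or a visit: "Compare the efficacy of ROC and CBT on binge eating over the duration of the study".

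The Analyses Plan in section 9 then gives binge eating "as measured by the EDE; EDE-Q and BES", examined "at mid-treatment, post-treatment and 6-months post-treatment timepoints. LME models with dummy-coded indicators for planned treatment comparisons between ROC and CBT". Counts and scales are modelled separately: "The GLME for counts of binge episodes and LME model for continuous symptom inventories provide maximum likelihood parameter estimates". Each model adjusts for the baseline value of its own outcome. Time is a continuous term, and the group-by-time interaction is there to show whether a difference fades by the 6-month follow-up.

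The Measures part of section 9 describes the three instruments:

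- The EDE interview "is considered the gold-standard assessment for BED and has strong psychometric properties". It yields binge frequency among several other scores. No recall window is given for it.
- The EDE-Q binge questions refer to 28 days and yield either a number of episodes or a number of days. A further item counts loss of control without a large amount of food.
- The BES has 16 items. Eight describe behaviours and eight "describe feelings and cognitions associated with binge eating".

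The same part opens its narrative list with "The primary outcome measures are provided in more detailed below".

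**The concern.** The choice of primary outcome belongs in the protocol. Here the protocol makes that choice but leaves it as an unranked set. It does not say which instrument, which score or which model contrast answers Aim 2, or what follows if the instruments disagree.

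Two things are at stake. With no true difference, three chances at a binge-eating finding carry more than the error rate of one. With a true difference, a scale that is half feelings and cognitions may move differently from a count of episodes, and nothing says which result decides.

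Other parts of the protocol depend on the answer. Exploratory Aim 1 adds its moderator terms to the primary outcome models, and the monitoring table in section 15 calls for a yearly report on the power implications of dropout. Both need a designated outcome. The sentence that introduces the Measures list does not supply one, because it gives the primary label to measures that the aims place elsewhere.

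**Working it through.** The protocol states no significance level, power or sample-size calculation, so there is no figure to reproduce. The error rates below rest on an assumed two-sided 5% per test and assumed correlations.

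**1. What follows the primary-outcome sentence.** Eighteen measure headings come after it. They sort against the aims in section 6 and the Analyses Plan as follows:

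| Role | Measures | Count |
|---|---|---|
| Primary Aims 1 to 3 | EDE, BES, EDE-Q, anthropometry, dietary recalls, feasibility, acceptability | 7 |
| Secondary Aim 1 | AEBQ, WLT-II, psychophysiology, reward-based eating (RED-13) | 4 |
| Exploratory Aim 1 | Godin questionnaire | 1 |
| Eligibility and description | MINI (baseline only), demographics (baseline only), medical history | 3 |
| Not named in any aim's analysis | adherence, stop-signal task, dot-probe | 3 |

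7 + 4 + 1 + 3 + 3 = 18, so 11 of the 18 do not serve a primary aim.

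**2. Number of tests under Aim 2.** There is one longitudinal model per outcome, so the minimum is three tests, one per instrument. Choosing between EDE-Q scores would add to this.

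**3. Chance of at least one false positive.** For independent tests it is 1 − (1 − 0.05)³ = 1 − 0.857 = 14.3%. For equally correlated normal test statistics, simulation with 400,000 draws gives:

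| Correlation (assumed) | At least one p < 0.05 | At least one in favour of ROC |
|---|---|---|
| 0.3 | 13.5% | 6.8% |
| 0.5 | 12.5% | 6.3% |
| 0.7 | 10.9% | 5.5% |
| 0.8 | 9.8% | 4.9% |
| 0.9 | 8.4% | 4.2% |

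A single test would give 5% and 2.5%.

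**4. How often the instruments point different ways.** With no true difference, the chance that three equally correlated estimates do not all share a sign is 1 − [1/4 + (3/2π) arcsin r]. For r = 0.5 this is 1 − [0.25 + 0.477 × 0.524] = 50%. The same formula gives about 60% at r = 0.3, 38% at 0.7, 31% at 0.8 and 22% at 0.9.

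**5. Cost of keeping all three as primary.** Assume 60 per arm (at least 120 randomised; an equal split is not stated), a continuous outcome, a difference of 0.5 SD, and no dropout or clustering by treatment group. Power is Φ(d√(n/2) − z), with d√(n/2) = 0.5 × √30 = 2.739.

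- One outcome at 0.05: Φ(2.739 − 1.960) = Φ(0.779) = 78%.
- Three outcomes at 0.05/3 = 0.0167 each (Bonferroni): Φ(2.739 − 2.394) = Φ(0.345) = 64% per outcome.

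The sample size per arm for 80% power is 2(z + 0.842)²/d². This gives 2 × 2.802²/0.25 = 63 for one outcome and 2 × 3.236²/0.25 = 84 for three. These figures only illustrate scale, since the lead outcome proposed below is a count.

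**The case against.** The strongest reply is that the statistical analysis plan may settle multiplicity and the decision rule. The protocol says only that differences will be estimated and nowhere says that one positive instrument is enough. That is fair as to multiplicity rules. A reader might infer that the sponsor intends to claim success on whichever instrument is positive, and the text does not support that. What stands is that the protocol itself lists the primary measures and leaves them unranked.

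A second reply concerns size. A reader might count three instruments at three visits as nine tests, which gives 23% to 32% under similar assumptions (between-visit correlation 0.5). The Analyses Plan does not describe visit-by-visit testing. Visits enter one model per outcome, and the interaction has its own stated purpose. Three tests is the supportable count. The lower end of the error range may also be nearer the truth for the EDE and EDE-Q, since the questionnaire is there to obtain binge frequency with less burden than the interview.

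Third, a reader might infer that the BES tilts towards CBT, because CBT is described as "improving maladaptive thoughts surrounding eating, shape, and weight". The protocol undercuts this. Its account of ROC includes cognitive restructuring among the coping skills and relief of guilt about overeating among the goals of psychoeducation. The instruments measure different things, but no passage shows that they would favour different arms.

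Finally, the sentence on primary outcome measures can be read loosely as introducing the main measures, since baseline-only items cannot be efficacy outcomes, and it does not change which outcomes are analysed for Aim 2. It also does not cover the whole battery: about 12 of roughly 32 entries in Table 2 have no narrative description. It remains a wrong label that conflicts with the protocol's own aims.

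**Conclusion.** The point holds. Primary Aim 2 has three instruments of equal rank, a choice of scores within the EDE-Q, and no named contrast. At an assumed two-sided 5% per instrument, the chance of at least one false-positive binge-eating result is about 8% to 14% over assumed correlations of 0.9 to 0.3, so roughly 1.7 to 2.7 times the rate of a single test (8.4/5 and 13.5/5). Disagreement between instruments is a realistic prospect with no rule to resolve it. The direction of any disagreement cannot be predicted from the protocol.

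The mislabelled Measures list is a secondary inconsistency that should be corrected at the same time. This should be fixed. It does not undermine the design or the data collection, and the models already described can answer the aim once a lead outcome is named.

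**What to change.** In the Analyses Plan, decide Primary Aim 2 on one outcome: the binge-episode count from the EDE interview, with its recall window stated. The 28-day window is given only for the EDE-Q, so it cannot be assumed for the interview. The EDE is the natural lead because the protocol already ranks it highest as an assessment. It is also the only one of the three whose mid-treatment assessment agrees between the text and Table 2.

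Name one ROC-versus-CBT contrast from the longitudinal GLME. The overall group difference across the post-baseline visits fits the aim as worded in section 6. Define it explicitly as an average over the visits, because with a group-by-time term in the model the group coefficient alone is the difference at the zero point of the time scale. A single named visit is an alternative, but section 6 would then need rewording.

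Make the EDE-Q and BES supportive, with no efficacy claim resting on either alone. Correct the opening sentence of the Measures section so that only the measures of Primary Aims 1 to 3 are called primary.

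The cost is a few sentences and no new data. The downside is that a positive EDE-Q or BES result on its own would no longer support the Aim 2 claim. Keeping all three as primary with an adjusted level is possible but costs power, as shown in step 5.

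### Primary Aim 2 leaves three binge-eating instruments unranked and picks the shape of a continuous time term from the data, so the deciding arm comparison is not fixed

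*Protocol*

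**What the plan says.** Section 6 of the protocol states Primary Aim 2 as: "Compare the efficacy of ROC and CBT on binge eating over the duration of the study". It names no instrument, visit or summary measure.

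The Analyses Plan defines the outcome "as measured by the EDE; EDE-Q and BES", assessed "at mid-treatment, post-treatment and 6-months post-treatment timepoints". The Study Overview places these visits at about week 10, week 20 and week 44; treatment ends at week 20. The Measures section says that the EDE "is considered the gold-standard assessment for BED and has strong psychometric properties", but no ranking follows from this in the Analyses Plan.

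The models adjust for the baseline value of each outcome and contain "a continuous term for time selected after evaluating non-linearity". Two families are used: "The GLME for counts of binge episodes and LME model for continuous symptom inventories provide maximum likelihood parameter estimates". The arm comparison appears in two forms, a between-group difference in change and a group-by-time interaction. The purpose of the latter is stated: "Interactions of between-group indicator and time will assess whether differences in binge eating dissipate from active treatment compared to the 6-month follow-up timepoint". Neither form is named as the deciding test.

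**The concern.** Two things are left open that together decide what a positive Primary Aim 2 means.

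First, there are three instruments of equal standing. A reader of the results could not tell which one was meant to carry the aim, and a favourable result on any of them could be presented as success.

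Second, the time term. With baseline used as a covariate, three outcome visits remain, unequally spaced, two in the treatment phase and one 24 weeks after it ends. The shape of time determines which arm-by-time quantity is tested, and it is to be chosen after the data have been examined. If the choice is a straight line, one slope has to describe both phases, so it cannot separate the end-of-treatment effect from what happens afterwards. That separation is the question the interaction is meant to answer. If the choice is a quadratic, three visits are already fitted exactly, so the smooth term gains nothing over treating visit as a factor.

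**Working it through.** The protocol states no alpha, effect size or power figure for this aim, so there is no figure of its own to reproduce. The sums below are illustrations under stated assumptions.

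**1. Three unranked instruments**

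Inputs: 3 instruments (Analyses Plan); two-sided 5% per test (assumed); no true difference; one test per instrument; equal correlation r between the three test statistics (assumed).

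- Independent tests: 1 − 0.95³ = 0.143.
- Correlated tests: 1 − P(all three |Z| < 1.96), with Z trivariate normal.

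| r | Chance of at least one false positive |
|---|---|
| 0 | 14.3% |
| 0.5 | 12.5% |
| 0.7 | 10.9% |
| 0.8 | 9.8% |
| 0.9 | 8.4% |

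The high end of r should be included because the EDE and EDE-Q both measure binge frequency.

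**2. Choosing the time shape**

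For one instrument, taking the most favourable of four codings of the arm-by-time slope (weeks, log weeks, visit order, weeks squared) gives about 6.7% instead of 5% by simulation, with assumed visit correlations of 0.3 to 0.7. This is a worst case, with the choice made on the arm difference itself. A check on pooled data, blind to arm, would add little.

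**3. What a linear term does to the arm effect**

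Inputs: weeks t = 10, 20, 44. Mean 74/3 = 24.67. Deviations −14.67, −4.67, 19.33. Sum of squares 215.1 + 21.8 + 373.8 = 610.7. The arm difference at each visit is fitted by equal-weight least squares, as in a linear mixed model with complete data and equal within-person correlations.

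True effects (d, d, 0):

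- mean = 0.667d
- slope = (−14.67 − 4.67)d / 610.7 = −0.0317d per week
- fitted at week 20 = 0.667d + 0.0317d × 4.67 = **0.81d** (truth d)
- fitted loss, week 20 to 44 = 24 × 0.0317d = **0.76d** (truth d)

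The same steps for other patterns:

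| True effect at weeks 10, 20, 44 | Fitted at week 20 | True loss, week 20 to 44 | Fitted loss |
|---|---|---|---|
| d, d, 0.8d | 0.96d | 0.20d | 0.15d |
| d, d, 0 | 0.81d | 1.00d | 0.76d |
| 0.5d, d, 0.3d | 0.65d | 0.70d | 0.24d |
| 0.5d, d, 0 | 0.59d | 1.00d | 0.47d |

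In the third pattern the fitted line falls from 0.75d at week 10 to 0.40d at week 44.

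The average over the three visits is not distorted: for (d, d, 0) it is 0.667d under either coding. The distortion concerns visit-specific effects and the dissipation test. These sums apply to a linear model; in the count model d would be on the log scale and the fitted values would be approximate.

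**4. Parameter count**

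- Linear time: intercept, arm, time, arm-by-time = 4.
- Quadratic: adds time² and arm-by-time² = 6.
- Three-level visit: intercept, arm, 2 visit terms, 2 arm-by-visit terms = 6.

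The quadratic and the visit factor therefore fit the same visit means. The visit factor needs no selection step.

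**The case against.** **The analysis plan may settle this.** Time coding and multiplicity rules are often left to an SAP, which is not shown. That is fair as far as silence goes. But the protocol is not silent: it commits to three measures for a primary aim and to a data-selected continuous time term. Those are stated choices.

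**The protocol gives no any-of-three success rule.** True. The 8% to 14% describes what the wording permits, not a declared rule. A reader might go further and count every visit, or add the BMI and energy-intake outcomes of Primary Aim 3, and arrive at a much larger error rate. The documents do not support that. The Analyses Plan describes longitudinal models, not separate tests at each visit, and Aims 2 and 3 are stated as separate questions.

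**Non-linearity is to be evaluated, so a poor straight line may be rejected.** This stands. The bias arises only if linear time is kept, and it is small when little of the effect is lost (0.96d for d, d, 0.8d). No criterion is given for rejecting linearity, however, and at three visits the alternative is already saturated.

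**The choice may be blind to arm.** The text does not say either way. If it is blind, error inflation is minor, but the contrast to be tested is still not fixed in advance.

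**A reader might infer that the protocol expects the effect to fade.** It does not say so. It asks whether differences dissipate, and the fading patterns above are assumptions.

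**Three visits is not secure for every measure.** The Analyses Plan names three time points, but the EDE-Q binge items are also collected monthly, and the schedule table marks EDE-Q and BES during treatment, not at mid-treatment. The saturation argument is firm for the EDE, and for the other two only at the three named time points.

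**Conclusion.** The point holds. Nothing in the protocol names a deciding binge instrument, visit or contrast for Primary Aim 2, and the time term is open to selection without a rule.

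Its size is moderate. The instrument choice permits about 8% to 14% false positives in place of an assumed 5%, depending on an assumed correlation. The time-shape choice contributes little error if blind to arm and at worst about 6.7% for one instrument. The cost to estimation is conditional: if linear time is kept and the effect fades after treatment, the week-20 effect and the later loss are both understated, slightly with mild fading and substantially with complete fading. An average over the three visits would not be biased in this way with complete data.

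The case for changing the plan does not depend on severe bias. A visit factor answers the protocol's own dissipation question directly, and it removes a data-dependent step.

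**What to change.** Before any look at the outcome data by arm:

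1. Replace the data-selected continuous time term with visit as a three-level factor (mid-treatment, post-treatment, 6-month follow-up) and arm-by-visit terms, keeping the baseline value as a covariate.
2. Test dissipation as the arm effect at week 44 minus the arm effect at week 20.
3. Name EDE binge-episode frequency as the primary binge outcome, since the protocol itself gives the EDE the highest standing.
4. Pre-state one arm contrast on that outcome. Week 20 would target the end of treatment; the average over the three visits would match the aim as worded in section 6. Either is defensible, but one must be named.
5. Make EDE-Q and BES supportive.

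The cost is protocol wording, two extra mean parameters per model compared with linear time (none compared with a quadratic), and the loss of primary status for EDE-Q and BES. A week-20 contrast would also narrow an aim that is now stated over the whole study.

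Keeping all three instruments as primary with a Bonferroni split costs more. At an assumed 60 per arm and an assumed standardized difference of 0.5, before dropout and covariate gains, power falls from 78% at 5% to 63% at 0.05/3 = 1.67%.
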